### Randomization and Blindness

During the recruitment period, participants will be allocated 1:1 to two groups (*n* = 40) by computer-generated randomization procedures using opaque envelopes. A research assistant not involved in the study will prepare the envelopes before the study. After recording baseline measures, participants will be randomly allocated to either the intervention or the control group by the treating physicians, who will open the sealed opaque envelopes. In order to minimize selection bias, patients and assessors involved in the trial will be masked to the treatment allocation. All outcome measurements will be assessed by two observers who will be blinded to the treatment plan. Any disagreement will be resolved by reaching a consensus between the two. If no consensus can be reached, a third observer blinded to the treatment assignment and not involved in the clinical treatment plan will have the final decision. Finally, an independent investigator blinded to the treatment assignment will collect the data of outcomes and information of the group and analyze them.

### Interventions

Participants in both groups will be treated with the standard management according to the guidelines (30). In order to ensure the stability of administration speed and the stability of BP, patients allocated to the GTN group will undergo intravenous administration of GTN (5 mg GTN in 50 ml saline, with a speed of GTN 0.4 mg/h continued for 12.5 h/day, for 2 days) within 24 h of symptom onset. In the control group, 0.9% NS will be administered by continuous intravenous pumping with a speed of 4 ml/h continued for 12.5 h/day, for 2 days. Since no standard intravenous dose of GTN is available for AIS, the doses and administration of intravenous GTN are determined by following considerations. First, according to routine dosage of intravenous GTN, 0.3 mg/h (up to 20 mg/h) is applied. Second, because of the dose-dependent reductions in SBP (31) by GTN, we will use the similar low dose at 0.4 mg/h for 12.5 h/day to prevent excessive reduction of systemic BP for safety purposes. In addition, compared with intravenous administration, studies (20, 21, 25, 32) have shown that transdermal GTN patches (at a 0.4 mg/h rate for 12.5 h during a single application), in which there are about 75% of nitroglycerin systemically bioavailable after administration (33), reduce SBP by 5.8–13 mmHg after AIS that is within the range in the present study. Vital signs (i.e., BP, heart rate, body temperature, respiratory rate of the patients) and possible adverse drug reactions such as hypotension and headache, will be closely monitored during the whole treatment period. If the patients show a tendency to develop adverse reactions and complications, the trial shall be immediately stopped, and routine treatment shall be given.

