### Outcomes

#### Primary Outcomes (Safety Assessment)

The primary safety outcome is SBP <110 mmHg. The primary outcome SBP <110 mmHg was defined as average SBP <110 mmHg within 24 h after GTN has been started. BP will be measured every 15 min between 0 and 2 h after GTN is started, every 30 min between 2 and 12 h, every 120 min between 12 and 48 h, and twice a day after 48 h. The target levels of BP poststroke remain unclear within the available literature (34–37). The current AIS guidelines differentiate BP targets based on a variety of factors including whether the patient receives alteplase, undergoes mechanical embolectomy, and/or experiences a hemorrhagic conversion. Prior studies (34–37) found a U-shaped relation of BP with functional outcome: both low BP and high BP were associated with poor outcome. There is no clearly defined cutoff for low BP in patients with AIS. Previously identified nadirs such as the tipping point in the U-shaped association between BP and outcome also vary between 120 and 180 mmHg (34, 36). Because of this variability, according to prior studies, we will use the lowest 10th percentile as a cutoff, low SBP, namely, SBP <110 mmHg.

The secondary safety outcomes are headache. Headaches related to GTN were defined as follows: GTN responders are those who develop a mild to moderate headache (headache scores 3–6) within 5–15 min with a short-lasting duration (maximum of 30 min) and spontaneously recover within 1 h after administration of GTN without the need for any rescue medication (38). In addition, severe headaches (scores 7–10) or the use of analgesia for GTN-caused headaches will be accounted for as secondary safety outcomes. If patients experience severe headaches, vital signs (i.e., BP, heart rate, body temperature, respiratory rate of the patients) will be closely monitored, and a CT scan will be obtained to analyze the cause of the headache.

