### Statistical Analyses

All analyses are based on the intention-to-treat (ITT) principle, including all randomly enrolled subjects. Compared to the control group, if the GTN group did not have an increase in the incidence of adverse reactions and there was no difference in 90-day prognosis between the two groups, we would move forward with a phase 2 trial.

Categorical variables including the proportion of good functional outcomes and the frequency of adverse events will be presented as counts and percentages. χ^2^ test, Fisher exact test, or continuity correction will be used where appropriate for comparison between the two groups. If the continuous variables including NIHSS score and infarct volume conform to the normal distribution, results shall be indicated by mean ± standard deviation and tested by *t*-test, and if they do not conform to the normal distribution, results shall be indicated by median and interquartile range and tested by Mann–Whitney *U*-test. p < 0.05 will be considered statistically significant. SPSS 22.0 software (IBM Inc., Armonk, NY) will be used for statistical analysis.

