NO plays a pivotal role in preventing inflammation and attenuating oxidative stress after IRI, and, therefore, NO supplementation using NO donor drugs is a reasonable approach to minimizing the cerebral damage after ischemia. GTN is one of the most widely used exogenous NO donors in the clinic. Three studies (20–22) on transdermal GTN in acute stroke showed that GTN lowered peripheral and central BP, 24-h BP, pulse pressure, and augmentation index. However, RCTs ENOS (53) and RIGHT-2 (25) on transdermal GTN patch (5 mg) showed that there was no significant change in functional or secondary outcomes measured at day 90. In a prespecified subgroup analysis of participants within 6 h of stroke presentation in the ENOS trial, those who received GTN had a favorable improvement in functional outcomes, less death and disability, and improved cognition (25). Transdermal GTN is a simple method to the delivery of GTN; however, not all of the drug released from the patch reaches the systemic circulation (54). Compared with intravenous administration, about 75% of nitroglycerin is systemically bioavailable after patch administration (55). The reason for lost drug is related to retention at the application site, tissue binding, and breakdown (33). The development of an intravenous form of nitroglycerin has further enhanced the role of nitrates in the therapy of cardiovascular disorders. Intravenous form of nitroglycerin permits prompt initiation of therapy and rapid attainment of high systemic levels (56). Although there is concern that lowering BP may worsen outcomes in the context of carotid stenosis, an analysis of the ENOS trial demonstrated that transdermal GTN appeared safe in both ipsilateral and bilateral stenoses (25). Considering that both GTN and NO (57) have a very short half-life in the body, an intravenous form of nitroglycerin with rapid dose titration is both feasible and safe. This may be the best method in a clinical trial for stroke patients to receive targeted cerebral NO donors. Prior clinical trials on the continuous application of nitroglycerin patches showed that 24-h continued use of GTN results in developing tolerance in the majority of patients with stable angina and suggested that “intermittent” therapy may provide a more rational approach to therapy. With removal of the patch for 10–12 h in each 24-h period, this will provide a patch-free period, which may allow the reestablishment of sensitivity (27–29). The daily dose at 5 mg/day [0.4 mg/h (54)] was recommended in the two important RCTs ENOS and RIGHT-2 on transdermal GTN patch (25, 58). In order to rescue the ischemic penumbra that infarct completed within 48 h after stroke onset (59), GTN at a speed of GTN 0.4 mg/h for 12.5 h/day, which makes 5 mg/day in total, was used in the present study, for 2 days. We will determine whether intravenous GTN is safe and has the potential to improve functional outcomes in patients with AIS.

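### The 24-hour average SBP used as the primary safety outcome is insensitive to hypotension during the 12.5-hour infusion, and stopping early for low pressure makes it more so

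*Protocol article*

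**What the plan says.** The protocol article (Primary Outcomes) defines the event thus: "The primary outcome SBP <110 mmHg was defined as average SBP <110 mmHg within 24 h after GTN has been started". The reading schedule is dense at first and sparse later: "BP will be measured every 15 min between 0 and 2 h after GTN is started, every 30 min between 2 and 12 h", then two-hourly to 48 h. GTN runs for 12.5 h on each of two days, and entry requires SBP of at least 120 mmHg (Patient Population).

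Under Interventions, "possible adverse drug reactions such as hypotension and headache, will be closely monitored during the whole treatment period". The next sentence is the stop rule: "If the patients show a tendency to develop adverse reactions and complications, the trial shall be immediately stopped, and routine treatment shall be given". The same section cites patch studies showing that GTN can "reduce SBP by 5.8–13 mmHg after AIS that is within the range in the present study". The Discussion says that GTN and NO "have a very short half-life in the body".

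Under Statistical Analyses, all randomised patients are analysed by intention to treat. One condition for moving to phase 2 is "if the GTN group did not have an increase in the incidence of adverse reactions". No text counts a low reading during infusion, or a stop for low SBP, towards the primary outcome.

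**The concern.** The trial's main purpose is safety, and the risk it singles out is low SBP while GTN is running. The outcome chosen for that risk averages over a window nearly twice as long as the infusion. If SBP recovers once the pump is off, off-drug readings pull the average back towards the entry level. A patient whose infusion is stopped for low SBP contributes even more off-drug readings and remains in the denominator.

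The primary result could therefore be close to zero in a trial where hypotension on drug was not rare. As an illustration with assumed counts: with 20 patients per arm, if 3 GTN patients were stopped within 2 h for SBP of 90 to 109 and then recovered, the primary outcome could read 0/20 (95% CI 0 to 16.8%), although 3/20 (3.2 to 37.9%) had SBP below 110 on drug.

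**Working it through.** **Inputs from the article.** Threshold 110; window 24 h; infusion 12.5 h; entry SBP at least 120; cited falls 5.8 to 13 mmHg; reading schedule as above.

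**Assumptions.** SBP returns to the entry level off drug (the article gives no recovery time), the second infusion starts no earlier than 24 h, and readings continue to 24 h after a stop. The article does not say whether the average weights readings or time, so both are shown.

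**Number of readings.** 8 (first 2 h) + 20 (2 to 12 h) + 6 (12 to 24 h) = 34, of which 28 fall within the infusion. An event needs a sum below 34 × 110 = 3740.

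**Full infusion, no stop.** With entry level B and fall D:
- By readings: B − D × 28/34 < 110. For D = 13, B < 120.7. At B = 120 the mean is (28 × 107 + 6 × 120)/34 = 109.3, an event; at B = 121 it is 110.3, no event.
- For D = 10 or 5.8 at B = 120, the means are 111.8 and 115.2, no event.
- By time: B − D × 12.5/24 < 110. For D = 13, B < 116.8, which the entry criterion rules out. At B = 120 the mean is (12.5 × 107 + 11.5 × 120)/24 = 113.2.

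At higher entry levels, on-drug SBP throughout a full infusion must be below the following for an event:

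| Entry SBP | By readings, (3740 − 6B)/28 | By time, (2640 − 11.5B)/12.5 |
|---|---|---|
| 120 | 107.9 | 100.8 |
| 130 | 105.7 | 91.6 |
| 140 | 103.6 | 82.4 |
| 150 | 101.4 | 73.2 |

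**Infusion stopped early.** With k readings at S on drug and 34 − k at B off drug, the mean is (kS + (34 − k)B)/34.
- S = 107, B = 120: stop at 2 h (k = 8), 116.9; at 4 h (k = 12), 115.4; at 6 h (k = 16), 113.9. An event needs k of at least 27, the reading at 11.5 h.
- Without fixing B, a patient at S = 90 until the stop is event-free if off-drug SBP averages at least (3740 − 90k)/(34 − k): 112.7 after a 1 h stop, 116.2 after 2 h, 120.9 after 4 h.
- Exception: 90 mmHg for 2 h with recovery only to 115 gives (8 × 90 + 26 × 115)/34 = 109.1, an event.

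**How much is due to the stop.** A simulation used a mean fall of 10 mmHg (SD 10), reading SD 8, recovery 30 min after the stop, and entry SBP centred on 125, 135 or 150 with values below 120 excluded (all but the 10 mmHg fall assumed). Patients were stopped at the first, or the second consecutive, on-drug reading below 110. Had their infusions run on, 11 to 32% of them would have scored an event by readings; once stopped, 0.0% did. With mean falls of 20 or 30 mmHg the unstopped figures were 21 to 78%, and the stopped figure stayed at 0.0%. At the fall the article expects, the averaging alone misses most of these patients, and the stop removes the rest.

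**The case against.** The averaged outcome is a stated choice. The article justifies the 110 cut-off by the U-shaped relation between blood pressure and functional outcome, and a brief dip that is quickly reversed is correctly not a low 24-h average. This stands, and it is why the definition should be kept.

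A reader might infer that the stop rule is what hides hypotension. The documents do not support that: within the cited falls, an unstopped patient entering at 121 or more is already event-free. The stop matters alone only near 120 or for larger falls. The cited falls come from patch studies, and individual falls on intravenous GTN could exceed them, but the article gives no figure.

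A reader might also infer that the signal is lost to the trial. It is not. Hypotension is a monitored adverse reaction, adverse-event frequencies are compared between arms, and the phase 2 decision refers to adverse reactions, not explicitly to average SBP.

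Finally, the stop rule says the trial, not the infusion, is stopped, and it gives no SBP trigger. Reading it as one patient's infusion is an inference from the routine treatment that follows. An exact trigger may well sit in the full protocol, so its absence here is not held against the plan.

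**Conclusion.** The point holds as a limit on what the primary outcome can show. Given recovery to the entry level off drug, the largest cited fall scores an event after a full infusion only for entry SBP between 120 and about 120.7 by readings, and for no eligible patient by time. A patient stopped early for low SBP will usually be event-free; the exceptions are deep or prolonged falls, or incomplete recovery, in patients entering near 120.

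The consequence is a reassuring primary result that may contradict the adverse-reaction table. It does not follow that the primary outcome should be replaced by a count of low readings, because such a count picks up ordinary variation in patients entering near the threshold. The sample size, based on a 10 mmHg mean difference, is unaffected.

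**What to change.** Keep the 24-h average as defined, and state whether it is by readings or by time. Add two named key safety outcomes, reported by arm beside it:

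- (a) SBP below 110 on two consecutive scheduled readings during the first infusion, up to and including the stop, with each case listed alongside entry SBP.
- (b) Infusion stopped for low SBP. This catches a patient stopped at the first low reading, whom (a) would miss. Report it separately, not within a composite, because patients are "randomly allocated to either the intervention or the control group by the treating physicians, who will open the sealed opaque envelopes", so the decision to stop may be made by someone who knows the arm.

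In Interventions, say that the patient's infusion is stopped and that BP recording continues to 24 h. State that a low rate on the 24-h average alone will not be read as absence of hypotension.

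The cost is a short amendment, with no extra patients, visits or scheduled readings. The downside is background events in (a). With no drug effect, an assumed reading SD of 5 to 10 mmHg and an assumed correlation of 0 to 0.5 between successive readings, at least one such pair among 28 readings occurs in about 1 to 67% of patients with mean SBP 120, at most 9% at 130 and at most 0.2% at 140. The control arm is the reference for that rate.

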### Outcomes

#### Primary Outcomes (Safety Assessment)

The primary safety outcome is SBP <110 mmHg. The primary outcome SBP <110 mmHg was defined as average SBP <110 mmHg within 24 h after GTN has been started. BP will be measured every 15 min between 0 and 2 h after GTN is started, every 30 min between 2 and 12 h, every 120 min between 12 and 48 h, and twice a day after 48 h. The target levels of BP poststroke remain unclear within the available literature (34–37). The current AIS guidelines differentiate BP targets based on a variety of factors including whether the patient receives alteplase, undergoes mechanical embolectomy, and/or experiences a hemorrhagic conversion. Prior studies (34–37) found a U-shaped relation of BP with functional outcome: both low BP and high BP were associated with poor outcome. There is no clearly defined cutoff for low BP in patients with AIS. Previously identified nadirs such as the tipping point in the U-shaped association between BP and outcome also vary between 120 and 180 mmHg (34, 36). Because of this variability, according to prior studies, we will use the lowest 10th percentile as a cutoff, low SBP, namely, SBP <110 mmHg.

The secondary safety outcomes are headache. Headaches related to GTN were defined as follows: GTN responders are those who develop a mild to moderate headache (headache scores 3–6) within 5–15 min with a short-lasting duration (maximum of 30 min) and spontaneously recover within 1 h after administration of GTN without the need for any rescue medication (38). In addition, severe headaches (scores 7–10) or the use of analgesia for GTN-caused headaches will be accounted for as secondary safety outcomes. If patients experience severe headaches, vital signs (i.e., BP, heart rate, body temperature, respiratory rate of the patients) will be closely monitored, and a CT scan will be obtained to analyze the cause of the headache.

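### The 24-hour average SBP takes in readings after an early stop and off drug, so low pressure that is promptly stopped and recovers is usually not a primary safety event

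*Protocol article*

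**What the plan says.** Under Primary Outcomes (Safety Assessment), the protocol article fixes the primary event: "The primary outcome SBP <110 mmHg was defined as average SBP <110 mmHg within 24 h after GTN has been started". The same section gives the reading schedule. It starts with "BP will be measured every 15 min between 0 and 2 h after GTN is started", then moves to every 30 minutes until 12 h and every 2 hours until 48 h. It does not say whether the average is a plain mean of readings or is weighted by time.

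Under Interventions, GTN runs "with a speed of GTN 0.4 mg/h continued for 12.5 h/day, for 2 days". The section says that "possible adverse drug reactions such as hypotension and headache, will be closely monitored during the whole treatment period", and then orders: "If the patients show a tendency to develop adverse reactions and complications, the trial shall be immediately stopped, and routine treatment shall be given".

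Under Statistical Analyses: "All analyses are based on the intention-to-treat (ITT) principle, including all randomly enrolled subjects". No text limits the average to readings on the infusion or before a stop, and none counts a stop for low pressure as a primary event. The rule for moving to phase 2 does not use the 24-hour average. It asks, among other things, "if the GTN group did not have an increase in the incidence of adverse reactions".

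Patients must enter with SBP of at least 120 mmHg (inclusion criteria). The treating physicians open the allocation envelopes (Randomization and Blindness).

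**The concern.** The stop rule and the outcome definition pull against each other. If staff follow the stop rule, SBP is expected to recover, and the recovered readings enter the same 24-hour average that defines the event. The scheduled off-drug hours, 24 − 12.5 = 11.5, enter it for everyone.

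A low primary event count could therefore mean that this dose seldom lowers SBP too far, or that staff stopped the infusion in time. These say different things about whether the dose is tolerable, and safety is the trial's primary purpose.

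**Working it through.** The plan gives no expected rate of the primary event, so there is no figure of its own to reproduce here. Its sample size (16 per group for a 10 mmHg difference with SD 10) concerns mean SBP and is not affected.

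**Inputs from the article.** Readings from 0 to 24 h: 9 (0–2 h, every 15 min) + 20 (2.5–12 h, every 30 min) + 6 (14–24 h, every 2 h) = 35. Of these, 29 fall within the 12.5 h infusion and 6 (17%) after it. By time, 11.5/24 = 48% is off drug, taking the second infusion to start no earlier than 24 h.

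**Assumptions, not in the documents.** SBP sits at a low level L from 0 h through hour d, then steps to a recovered level R. The 0-h reading is counted as low.

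**Formulas.** With k readings at the low level (5 for d = 1 h, 13 for d = 4 h, 29 for d = 12.5 h):
- plain mean = [kL + (35 − k)R]/35
- time-weighted mean = [dL + (24 − d)R]/24

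**Worked case, L = 90, R = 120.**
- Not stopped: (29×90 + 6×120)/35 = 95.1; (12.5×90 + 11.5×120)/24 = 104.4. Event on both.
- Stopped at 1 h: (5×90 + 30×120)/35 = 115.7; (90 + 23×120)/24 = 118.8. Non-event on both.
- Off-drug time alone raises the average from 90 by 5.1 (plain) or 14.4 (time-weighted), which leaves an event. The stop adds a further 20.6 or 14.4, which removes it.

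**Other levels (plain / time-weighted).**

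| Low level | Not stopped, R = 120 | Not stopped, R = 130 | Not stopped, R = 140 | Stopped at 1 h, R = 120 |
|---|---|---|---|---|
| 80 | 86.9 / 99.2 | 88.6 / 104.0 | 90.3 / 108.8 | 114.3 / 118.3 |
| 90 | 95.1 / 104.4 | 96.9 / 109.2 | 98.6 / 114.0 | 115.7 / 118.8 |
| 95 | 99.3 / 107.0 | 101.0 / 111.8 | 102.7 / 116.6 | 116.4 / 119.0 |
| 100 | 103.4 / 109.6 | 105.1 / 114.4 | 106.9 / 119.2 | 117.1 / 119.2 |

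On the plain mean, every unstopped case in the table is an event and every case stopped at 1 h is not. On the time-weighted mean that contrast holds throughout only at R = 120. At R = 130 the unstopped patients at 95 and 100 are already non-events, and at R = 140 so is the one at 90.

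**Limits of the masking (stopped patients, L = 90).**
- 4 h delay, R = 120: (13×90 + 22×120)/35 = 108.9; (360 + 2400)/24 = 115.0. The plain mean still catches it.
- Stopped at 1 h, R = 115: (450 + 3450)/35 = 111.4; (90 + 2645)/24 = 114.0. Non-event.
- Stopped at 1 h, R = 112: (450 + 3360)/35 = 108.9; (90 + 2576)/24 = 111.1. Event on the plain mean only.

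**Within the article's own effect range.** Interventions cites studies in which transdermal GTN was found to "reduce SBP by 5.8–13 mmHg after AIS that is within the range in the present study". A 13 mmHg fall held through the infusion lowers the plain mean by 13×29/35 = 10.8 and the time-weighted mean by 13×12.5/24 = 6.8. From an entry SBP of 120 or more, an unstopped patient is a plain-mean event only if entry is below about 120.8, and is never a time-weighted event. At exactly 120 (low level 107) the unstopped averages are 109.2 / 113.2; stopped at 1 h they are 118.1 / 119.5.

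**The case against.** The strongest reply is that a 24-hour average is meant to pick up sustained low pressure. Kept under intention to treat, it describes the strategy of giving GTN and stopping when needed, and a corrected dip is rightly a non-event. That stands as a description of what the average measures, and it is why the average should be kept. It does not let a low count speak for the dose itself.

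A reader might infer that any given reaction is an event if the infusion runs on and a non-event if staff act. The documents do not support that as a general statement. It depends on the averaging method, which is not stated, and on the recovery level: on the time-weighted mean many unstopped patients are non-events too. A dip that recovers by itself is diluted in the same way, so part of the effect belongs to averaging and not to the stop rule.

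A reader might also infer that the phase 2 decision is compromised. That is not supported either. The decision uses the incidence of adverse reactions, hypotension is named as one, and a stopped patient may well be recorded there.

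Finally, the order to stop the trial could be read as ending use of that patient's later readings. Then 1 h at 90 averages 90 and is an event. The wording of the outcome, an average within 24 h, points the other way, but the article does not settle it.

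**Conclusion.** The point holds in a limited form. Read literally, the plan usually scores low SBP that is promptly stopped and recovers to about 115 mmHg or more as a primary non-event. On a plain mean, the same patient left at 80–100 mmHg through the infusion would be an event for recovery levels of 120–140. On a time-weighted mean, off-drug time can already hide the episode when recovery is to 130 or more.

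How often this would occur is unknown, because the documents give no rate of low SBP; the levels, durations and recovery values above are assumptions. Within the cited average falls it matters only for entry SBP close to 120. Individual falls may be larger, but no distribution is given. The harm is confined to how the primary safety result is read. With about 20 patients per arm, a few such patients could change that reading, and the remedy is cheap, so it is worth making.

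**What to change.** Keep the 24-hour average SBP <110 mmHg and state that it is the plain mean of the scheduled readings, counted from the start of study infusion in both arms. Report beside it, by arm:

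- (a) average SBP <110 over readings on study infusion, up to any stop;
- (b) any infusion stop, fluid bolus or pressor within 24 h that was prompted by a recorded SBP <110.

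Base the primary safety conclusion on the three together. The patient at 90 who is stopped at 1 h then averages 90 under (a) and also appears under (b).

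The cost is a few sentences in the outcome definition and two table rows. The SBP readings are already scheduled; the reason for a stop or treatment must be recorded. Clinical care does not change. There are two downsides. Component (a) rests on few readings after a very early stop. Component (b) is partly clinician-driven: the treating physicians open the envelopes and may stop GTN more readily than saline at the same pressure. The recorded-SBP trigger limits this but does not remove it, so (b) is shown separately and not merged into the 24-hour average.

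### The primary safety outcome averages SBP over the first 24 h, which mixes the first infusion with drug-free hours and leaves most or all of the second infusion out

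*Protocol article*

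**What the plan says.** All references are to the protocol article.

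- **Outcome** (Primary Outcomes): SBP below 110 mmHg "was defined as average SBP <110 mmHg within 24 h after GTN has been started".
- **Exposure** (Interventions; the Study Design section agrees): GTN is given "with a speed of GTN 0.4 mg/h continued for 12.5 h/day, for 2 days". Controls receive saline on the same timetable.
- **Readings** (Primary Outcomes): "BP will be measured every 15 min between 0 and 2 h after GTN is started, every 30 min between 2 and 12 h", then "every 120 min between 12 and 48 h, and twice a day after 48 h".
- **Gap between infusions** (Discussion): no start time is given for the second infusion. The rationale for intermittent dosing rests on patch studies: "With removal of the patch for 10–12 h in each 24-h period".
- **Pharmacology** (Discussion): "both GTN and NO (57) have a very short half-life in the body".
- **Other capture of hypotension**: Interventions lists hypotension among the adverse drug reactions that "will be closely monitored during the whole treatment period". Statistical Analyses compares adverse event frequencies between the groups. Neither section gives an SBP threshold for that event.

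**The concern.** The main safety question is whether intravenous GTN lowers SBP too far while it is being given. The outcome window is fixed at 24 h, and the exposure is two infusions of 12.5 h on separate days. Two consequences follow. Recovered pressures after the first infusion can offset low pressures during it, since the drug is described as clearing quickly. Low pressures during the second infusion, which is half of the planned dose, hardly enter the outcome or do not enter it at all. An average also hides short lows, and no on-infusion component is defined beside it. With about 20 patients per arm, a few unscored episodes could change how the primary result reads.

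**Working it through.** The plan states no expected rate for this outcome, so there is no event figure to reproduce. The dose arithmetic does reproduce: 0.4 mg/h × 12.5 h = 5 mg per day, and 2 × 5 = 10 mg in total, half of it in each infusion.

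**1. Readings in the 24-h window.** Every 15 min to 2 h gives 8, every 30 min to 12 h gives 20, and every 120 min to 24 h gives 6. The total is 34, of which 28 fall during the first infusion. A time-0 reading would make it 35, but it precedes any drug effect.

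**2. Weight of drug-free time**, if the second infusion starts at 24 h or later:
- time-weighted: (24 − 12.5)/24 = 11.5/24 = 48%
- plain mean of scheduled readings: 6/34 = 18%

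With a 10 h gap these become 10/24 = 42% and 5/34 = 15%.

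**3. What the dilution does.** Assume full recovery to the entry level off drug. The on-drug fall needed for an event is (entry SBP − 110)/(on-drug weight), with weight 12.5/24 = 0.521 or 28/34 = 0.824.

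| Entry SBP | Fall needed, on-drug mean alone | 24-h time-weighted | 24-h plain mean |
|---|---|---|---|
| 120 | 10 | 19.2 | 12.1 |
| 130 | 20 | 38.4 | 24.3 |

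Entry requires SBP of at least 120 mmHg, and Interventions cites falls of 5.8 to 13 mmHg. Take entry at 120 and the upper fall of 13, an on-drug mean of 107. The 24-h average is 0.521 × 107 + 0.479 × 120 = 113.2 time-weighted (no event), or (28 × 107 + 6 × 120)/34 = 109.3 as a plain mean (event). Dilution therefore matters a good deal under one averaging rule and modestly under the other.

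**4. Short lows.** Take 90 mmHg for the first 4 h, then 130 mmHg (illustrative):
- time-weighted: (4 × 90 + 20 × 130)/24 = 123.3
- plain mean, 34 readings: (12 × 90 + 22 × 130)/34 = 115.9
- plain mean with a time-0 reading also at 90: (13 × 90 + 22 × 130)/35 = 115.1

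No event on any version. Here pressure recovers while the drug is still running, so this shows averaging hiding a short low, not drug-free dilution.

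**5. Second infusion.** A gap of 10 to 12 h puts its start at 12.5 + 10 = 22.5 h to 12.5 + 12 = 24.5 h. With the earliest start, 1.5 h of 12.5 h is inside the window, so 11/12.5 = 88% is outside. With a start at 24 h or later, 100% is outside. Even at the earliest start, that 1.5 h carries 1.5/24 = 6.25% of a time-weighted average. With SBP at 120 otherwise, it would have to fall by 10/0.0625 = 160 mmHg to score an event, which is impossible. Low SBP confined to the second infusion is thus not scored in any realistic case.

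**6. Readings available for the second infusion.** With a start at 24 h, readings at 24, 26, …, 36 h give 7, or 6 without the one at the start.

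**The case against.** A 24-h mean is a legitimate measure of sustained low pressure, and several objections to a harsher reading stand.

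- A reader might infer that nearly half of the outcome is always drug-free. That needs time-weighting, which the article does not state. Under a plain mean the share is about 18%. The averaging rule is a detail that an analysis plan commonly settles, so its absence is not raised here.
- A reader might infer that the whole second infusion is certainly excluded. No start time is stated, so only most or all of it can be claimed.
- A reader might infer that the trial is set up to conclude safety. Hypotension is also monitored as an adverse reaction over the whole treatment period. The stated condition for phase 2 rests on the incidence of adverse reactions and 90-day prognosis. The weakness is in one outcome, though it is the primary one, and the adverse-event route lacks a threshold.
- Two-hourly readings do not contradict the promise of close monitoring, which names no frequency. Timing from GTN start is only loose wording for controls, whose matched saline gives an evident time zero.
- The 4 h profile is invented, and Interventions says the trial is stopped for patients tending towards adverse reactions. That may make four hours at 90 mmHg unlikely, but it does not rescue the average: an early stop adds more recovered readings to it.

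What remains is the window itself. No detail in an analysis plan cures a stated 24-h window laid over a two-day exposure.

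**Conclusion.** The point holds as a should-fix. The primary outcome pools the first infusion with about 11.5 drug-free hours (48% of the weight if time-weighted, about 18% as a plain mean), and 88% to 100% of the second infusion falls outside it. Short on-drug lows, and low SBP confined to the second infusion, do not score as primary events. The second-infusion figure assumes a 10 to 12 h gap borrowed from the patch rationale. The thresholds in the table assume full off-drug recovery to the entry level, and the SBP profiles are illustrations, not predictions. The point does not show that the trial would miss hypotension altogether, since adverse reactions are reported as well.

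**What to change.** Keep the 110 mmHg cutoff but evaluate the primary outcome over the study-infusion periods of both days, timed from the start of the study infusion in both arms. One form is a time-weighted mean SBP below 110 mmHg during either infusion. State the planned start of the second infusion, and whether an infusion stopped early is averaged over the time actually infused.

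Add as a prespecified companion any scheduled reading below 110 mmHg during either infusion that is confirmed on the next reading. This is needed because an infusion-period mean still misses the 4 h example: (4 × 90 + 8.5 × 130)/12.5 = 117.2. Making a confirmed reading the sole primary event is more debatable. The article takes 110 mmHg from a lowest-10th-percentile cutoff in prior studies, and whether that suits single readings or averages cannot be checked here. Keep the 24-h average as a secondary measure.

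The cost is small, because all of this uses readings already planned to 48 h. Expect somewhat more events in both arms, including brief dips in controls under the companion measure; the documents give no basis for estimating how many. The second-infusion estimate will be less precise, with about 7 readings against 28 in the first.
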